## Abstract

**Background:**

Approximately 10% to 12% of New Zealand young people (and 21% of Maori young people) have long-term physical conditions and are more likely to develop psychological problems, particularly anxiety and depression. Delayed treatment leads to worse management of physical conditions, school absence, and poorer long-term outcomes. Recently, electronic health (eHealth) interventions have been shown to be as good as face-to-face therapy and biofeedback techniques have been shown to enhance relaxation during the treatment of anxiety. In addition, young people with long-term physical conditions have expressed a preference for more technologically based support, including game-based interventions, to deal with psychological issues, particularly anxiety.

**Objective:**

The aim of this study is to develop a prototype game-based eHealth intervention to address anxiety in young people with long-term physical conditions. The game will be based on the principles of cognitive behavior therapy (CBT) and will integrate a module of biofeedback-based relaxation.

**Methods:**

During the first phase of the study, up to 48 young people with long-term physical conditions aged 13 to 18 years, attending a tertiary pediatric hospital will be invited to participate in a 3-stage series of co-design workshops. Following the design, development, and refinement of a working prototype, during the second phase of the study, a further 20 young people with long-term physical conditions and anxiety will be recruited from the same location to participate in an open pilot trial to evaluate its acceptability, usability, and preliminary efficacy.

**Results:**

Changes in anxiety will be measured using the Generalized Anxiety Disorder 7-item scale (GAD-7) and the Spence Child Anxiety Scales (SCAS) at the end of every module (recommended to be completed weekly), post intervention, and 3 months later. Usability of the intervention will be measured using the System Usability Scale (SUS) and by measuring frequency and quantity of use of the intervention. Acceptability of the intervention will be assessed using brief, open-ended questionnaires and semi-structured interviews, the data from which will be analyzed using a general inductive approach. Recruitment to the study commenced in January 2017 and data collection will be completed by the end of December 2017.

**Conclusions:**

If acceptable and useful, this game-based eHealth intervention may offer a cost-effective and clinically useful intervention for addressing the psychological needs of over 16,000 young people with long term health conditions in New Zealand.

**Trial Registration:**

Australian New Zealand Clinical Trials Network Registry (ANZCTR): ACTRN12616001253493p; https://www.anzctr.org.au/Trial/Registration/TrialReview.aspx?id=371443 (Archived by WebCite at http://www.webcitation.org/6sYB716lf)

## Introduction

Long-term physical conditions are increasingly common in children and young people and those that last more than 3 months and impair functioning affect 10% to 12% of children globally [1]. These conditions include asthma, diabetes, epilepsy, and obesity, among others [2,3]. The prevalence of long-term physical conditions in childhood is increasing [4] and in some high-income countries, due to improvements in hygiene, immunization, and access to medical care, it is greater than that of acute illness [5].

Psychological problems, especially anxiety, are more likely in these individuals such that long-term physical conditions in children have consistently been associated with an increased risk of psychological problems [6-11], particularly anxiety which has been identified in up to 40% of these individuals [12]. The likelihood of anxiety is related to young people’s developmentally linked internal ability to manage stress, to family factors, and the cumulative allostatic load-related impact of illness and treatment, particularly distress and pain [13,14]. Anxiety and other psychological problems can occur during or even following the completion of medical (eg, cancer) treatment [15] and may be associated with school absence, poor academic performance, and lower health-related quality of life [16,17]. Left untreated, anxiety disorders tend to have a chronic and unremitting course [18] and tend to increase the risk for adult psychiatric disorders, including depression and substance use disorders [19].

Access to, and effectiveness of, treatments for these problems are currently limited. Psychological problems are traditionally addressed using psychotherapies such as cognitive behavior therapy (CBT) and pharmacotherapy (eg, anxiolytic or antidepressant medication). There is limited evidence that these therapies are effective for children with long-term physical conditions [20]. Psychotherapies are often not accessible and although 60% of children with anxiety who receive CBT show an adequate treatment response [21], there does appear to be room for improving current treatment.

With the increasing popularity of smart technology, release of app-based interventions, and calls from international organizations such as The Lancet Global Mental Health Group [22] for the introduction of innovative and accessible cognitive and behavioral strategies to treat anxiety, depressive, and other common mental health problems, electronic health (eHealth) interventions may have a useful role to play in addressing common mental health problems in young people with long-term physical conditions. Health games, such as Smart, Positive, Active, Realistic, X-factor Thoughts (SPARX) [23], have already been shown to be as good as face to face treatment for addressing depression in young people. Similar interventions such as Body Signs, Relaxation, Active Helpful Thoughts, Victory Over Your Fears, Enjoy (BRAVE) online [24] exist to treat anxiety but are not focused on health-related anxieties and are not widely available outside Australia. During a recent investigation by [name] and colleagues, young people with long-term physical conditions identified anxiety as the most significant psychological issue that they face. Together with their families and clinicians, they confirmed limited knowledge of and access to eHealth interventions and expressed support for the development of eHealth interventions targeted towards their needs [25].

Traditional psychological therapies often include a component of psychologically or chemically induced relaxation and there is increasing evidence that newer, more technologically-based forms of therapy, such a biofeedback, may achieve similar results, either alone or in combination with traditional therapies [26]. Furthermore, some biofeedback interventions have already been combined with game-based technology to reduce stress or treat behavior disorders [27]. Biofeedback involves the use of electrical or electro-mechanical equipment to measure physiologic processes occurring in a person and then feed this information back to them to develop a greater awareness and ability to control changes within their bodies with and without equipment [28] and improve health and performance [29]. There are a number of types of biofeedback including heart rate variability (HRV), electroencephalography (EEG), and pneumography (PNG). HRV is already used by some pediatric mental health teams in New Zealand (personal communication from [name], Starship Hospital, Auckland) and a recent systematic review by [name] supported further research into HRV biofeedback as a treatment for anxiety (in press).

The aims of this study are (1) to develop a prototype game-based eHealth intervention for treating anxiety in young people with long-term physical conditions via co-design with end-users at Starship Hospital; (2) to evaluate the acceptability of this intervention with its intended audience; (3) to evaluate the utility of this intervention with its intended audience; (4) to evaluate the efficacy of this intervention in a preliminary manner; and (5) to evaluate the feasibility of delivery of this intervention with its intended audience.

## Methods

### Research Strategy

The study will employ a mixed-methods design to co-design, produce, and test a prototype game-based eHealth intervention for treating anxiety in young people with long-term physical conditions.

### Study Design

The study will involve 2 phases. During the first phase, a prototype game-based eHealth intervention will be designed and refined via a co-design process with young people with long-term physical conditions attending a tertiary pediatric hospital in Auckland, New Zealand. Three stages of iterative consultation are planned, with 4 focus groups of up to 12 participants at each stage. At least one focus group at each stage will be arranged for Māori young people to ensure that, in the spirit of biculturalism, the intervention is culturally acceptable to them. By the end of this phase, a working prototype that is ready for pilot testing will be created and refined to ensure it is compatible with end-user expectations. During the second phase, an open pilot trial will be undertaken with 20 young people with long-term physical conditions and anxiety from the same hospital. Each will be loaned a portable device (iPad or similar tablet) on which the prototype intervention, questionnaires, and scales will be preloaded. They will be given up to 8 weeks to complete the intervention at a speed and frequency of their choosing.

### Study Population

Up to 48 young people with long-term physical conditions who are either inpatients or outpatients attending a tertiary pediatric hospital in Auckland, New Zealand will participate in focus groups during each stage of the first phase. Following this, 20 young people will then participate in the second phase, open trial.

#### Inclusion Criteria

Young people will be included in the first phase of the study if they are aged between 13 to 18 years, have any long-term physical condition over 3 months duration (eg, asthma, diabetes, cancer, cystic fibrosis), are of any ethnicity, do and do not have a known anxiety disorder, do or do not have any co-morbid mental health condition, can intellectually and physically use the device and intervention, and if they understand English and are able to provide informed consent or assent. Young people will be included in the second phase of the study if they meet all of the above criteria and have any symptoms of anxiety (not necessarily a diagnosed anxiety disorder).

#### Exclusion Criteria

Young people will be excluded from participation if they do not meet all of the inclusion criteria, if they have an intellectual disability or cannot speak English, or if they have recently undertaken or are undertaking CBT or other forms of psychotherapy, biofeedback therapy, or pharmacotherapy with anxiolytic medication, as these may confound the effectiveness of the prototype game-based eHealth intervention.

### Intervention

The prototype game-based eHealth intervention that will be co-designed with young people with long-term physical conditions will be a 4 to 8 module online, game-based intervention. Its content will be based on the principles of CBT and include an integrated or associated biofeedback-based relaxation component. It is anticipated that modules will take between 30 to 60 minutes each to be completed. Key elements that will be included are education about anxiety and coping strategies for anxiety, using one’s body (relaxation strategies), mind (recognizing unhelpful thoughts and cognitive restructuring), and actions (including graded exposure) to beat anxiety. The precise format and look of the prototype game-based eHealth intervention will be designed in conjunction with end users. The prototype intervention will be stored on a portable tablet, rather than available online or via a mobile app. Due to the co-design process that is being planned, the precise form and content of the intervention is not yet fully defined. However, key CBT-based principles including psychoeducation, relaxation, graded exposure to feared stimuli, and cognitive restructuring will be included. Further refinement of the intervention is likely on the basis of feedback from the pilot trial.

### Outcome Measures

The primary outcomes of the study are (1) acceptability of the prototype intervention, (ie, is the content and format acceptable to users), as assessed via a semi-structured interview following completion of the study at 8 weeks; (2) utility of the intervention (ie, is it useful), as assessed using the System Utility Scale (SUS) [30] following completion of the intervention at 8 weeks; and (3) feasibility of the intervention (ie, is it easy to deliver in a hospital/home setting), as assessed via a semi-structured interview following completion of the study at 8 weeks.

The secondary outcome of the study is efficacy (ie, does the intervention reduce anxiety and related issues). This will be assessed by measuring changes over time in the Generalized Anxiety Disorder, 7-item (GAD-7) [31], Spence Children’s Anxiety Scale (SCAS) [32], and the Pediatric Quality of Life Inventory (PedsQL) [33], as outlined in the schedule below (Table 1). The GAD-7 is a newer, brief scale for measuring anxiety that may be useful to incorporate into the final version of the intervention for ease of completion. The SCAS is a well-validated, 46-item self-report scale measuring child anxiety via an overall score and 6 subscales for panic/agoraphobia, social phobia, separation anxiety, obsessions/compulsions, fear of physical injury, and generalized anxiety. It has sound psychometric properties with internal consistency reported at 0.92 for the total child score. The PedsQL is a well-validated, 23-item self or parent report scale measuring quality of life. It has good internal consistency (0.88 for total scale), validity, and acceptability. It reliably distinguishes between healthy children and those with acute or long-term physical conditions.

### Statistical Methodology

Quantitative data will be analyzed using Microsoft Excel and Statistical Software Package (SPSS). Analyses will include basic descriptive statistics (eg, number of sessions completed, number of times device accessed, duration of use, changes in anxiety score, and demographic characteristics of the sample). McNemar’s chi-square tests and *t* tests will be used to assess the statistical significance of changes in anxiety scores over time. *P* values of less than .05 will be taken to indicate statistical significance and 95% confidence intervals will be used to establish the extent of any difference between pre- and post-measures. A sample size of 20 will enable detection of changes within the study group with effect sizes of 0.65 or more as statistically significance (alpha .05 with 80% power). Qualitative data will be analyzed using a general inductive approach. Collated text analyzed to identify emerging themes, which will then be independently coded by one researcher and a subset of 30% of results, will be cross-coded. NVIVO software will be used to handle transcripts.

**Table 1 table1:** Schedule of assessment procedures.

	Baseline	During intervention	Post intervention	3-month follow-up
Demographics	Yes			
GAD-7^a^	Yes	At the completion of each module	Yes	Yes
SCAS^b^	Yes	At the completion of each module	Yes	Yes
PedsQL^c^	Yes		Yes	
SUS^d^			Yes	
Online tracking		As used		
Semi-structured questionnaire			Yes	Yes

^a^GAD-7: Generalized Anxiety Disorder, 7-item.

^b^SCAS: Spence Children’s Anxiety Scale.

^c^PedsQL: Pediatric Quality of Life Inventory.

^d^SUS: System Utility Scale.

**Table 2 table2:** Timelines of the study.

Phase	Tasks	Timeframe
Phase 1	Ethics approval, securing of funding	September 2016 to December 2016
	Prototype development via co-design with young people and in conjunction with software company and engineers	January 2017 to December 2017
Phase 2	Recruitment of participants for open trial	September 2017 to December 2017
	Open trial	January 2018 to June 2018
	Analysis of results, write-up, and dissemination of study results	July 2018 to December 2018

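### McNemar's test is assigned to changes in anxiety scores, but no yes/no outcome is stated, and it stands beside a t test of the same change with no rule on which counts

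*Protocol article*

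**What the plan says.** All references are to the protocol article.

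- **Statistical Methodology** names two tests for one purpose: "McNemar’s chi-square tests and *t* tests will be used to assess the statistical significance of changes in anxiety scores over time". It sets significance at P below .05 and promises 95% confidence intervals for the pre/post difference.
- The sample-size basis, in the same section, is 20 participants and 80% power at alpha .05. The changes to be detected are given as "effect sizes of 0.65 or more as statistically significance".
- **Outcome Measures** makes efficacy the secondary outcome: "This will be assessed by measuring changes over time in the Generalized Anxiety Disorder, 7-item (GAD-7"), together with SCAS and PedsQL. SCAS is described as a "46-item self-report scale measuring child anxiety via an overall score and 6 subscales". No case, responder or cut-off definition is given for either anxiety scale.
- **Inclusion Criteria** admits to the open trial those who "have any symptoms of anxiety (not necessarily a diagnosed anxiety disorder"). No minimum score is set.

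**The concern.** McNemar's test compares two paired proportions. Its data are the counts of people who change category in each direction, so a category must exist first. The article attaches the test to scores and states no category, and the entry criterion does not supply one.

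Three things follow:

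- The cut-off would have to be chosen later, possibly with the data in view.
- Two significance tests would address the same change with no order between them. They differ greatly in power, and nothing says how to report one significant and one non-significant result.
- With 20 pairs, few people will change category. The chi-square form named in the article is then a poor approximation.

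At stake is how far the preliminary efficacy signal can be trusted. The Discussion says a randomised trial of a refined version is to follow.

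**Working it through.** **1. The plan's own figure.** Inputs from Statistical Methodology: n = 20, effect size 0.65, alpha .05, power 80%. I read the effect size as mean change divided by the SD of change, and alpha as two-sided; the article states neither.

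Paired t test: noncentrality = 0.65 × √20 = 2.907, df = 19, critical t = 2.093.

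- Power at n = 20: **78.7%**.
- Smallest n reaching 80%: 21 (80.9%).
- Effect detectable with 80% power at n = 20: 0.660.

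The stated figure is thus reproduced to rounding, as a paired t test on a continuous score. A standardised mean change does not by itself describe a McNemar test.

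**2. What McNemar's test would need.** Let b be the number moving from above to below a cut-off and c the number moving the other way.

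- Uncorrected chi-square = (b − c)² / (b + c), on 1 df.
- Exact two-sided P = 2 × Pr{Binomial(b + c, ½) ≤ min(b, c)}, capped at 1.

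When all changes go one way (c = 0):

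| b | Chi-square P | Exact P |
|---|---|---|
| 4 | .046 | .125 |
| 5 | .025 | .063 |
| 6 | .014 | .031 |

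The exact test needs at least 6 one-way changes for P < .05; the chi-square form needs 4.

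**3. Power of McNemar's test at the same effect.** The article gives neither a pre/post correlation r nor a cut-off, so both are assumed, with bivariate normal scores. A change of 0.65 SD of change equals 0.65 × √(2(1 − r)) baseline SDs: 0.650 at r = 0.5 and 0.503 at r = 0.7. Power is enumerated over all possible discordant counts at n = 20. Cut-offs are in baseline SDs from the baseline mean.

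| r | Cut-off | Pr(above→below) | Pr(below→above) | Chi-square power | Exact power |
|---|---|---|---|---|---|
| 0.5 | −0.33 | .322 | .067 | 45% | 31% |
| 0.5 | 0 | .305 | .063 | 43% | 29% |
| 0.5 | +0.5 | .228 | .045 | 35% | 16% |
| 0.7 | 0 | .241 | .048 | 36% | 18% |
| 0.7 | +0.5 | .188 | .037 | 29% | 9% |
| 0.5 | +1 | .133 | .024 | 18% | 3% |
| 0.7 | +1 | .114 | .021 | 13% | 1.5% |

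- For r from 0.5 to 0.7 and cut-offs within 0.5 SD of the mean: **29% to 45%** (chi-square) and **9% to 31%** (exact).
- Over a wider grid (r from 0.3 to 0.8, cut-offs from −1 to +1 SD): 9% to 51% and 1% to 39%.
- Expected number changing category: 20 × (.322 + .067) = 7.8 at r = 0.5, cut-off −0.33; 20 × (.188 + .037) = 4.5 at r = 0.7, cut-off +0.5; about 3 at +1 SD.

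**4. The open threshold.** Simulated with no true change (20,000 trials, n = 20, r = 0.5 and 0.7). Taking the smallest uncorrected McNemar P gives a type I error of about 13% over three cut-offs and 18% to 20% over five. With the exact test, the best of five stays below 5%.

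**5. A remedy that fails.** It is natural to restrict the analysis to baseline cases and then apply McNemar's test. In that subset c is zero by construction, so any 6 movers give P = .031. With no mean change and the cut-off at the baseline mean, Pr(above→below) = ¼ − arcsin(r)/(2π). At r = 0.5 this is .167, and Pr{Binomial(20, .167) ≥ 6} is about 10%. The corresponding false-positive rates are about 20% at r = 0.3 and 6% at r = 0.6, against a nominal 5%.

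**The case against.** The strongest reply is that this is a condensed article. Naming both tests may be shorthand for t tests on the scores plus McNemar's test on a caseness category, with the cut-off in the full protocol or analysis plan. That may be so, and a missing cut-off alone would not be a finding. What remains is that the printed sentence attaches a binary test to scores, beside a t test of the same change, and ranks neither.

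The second reply is that little is lost, and much of this stands. The t test named in the same sentence keeps the 78.7% on which the sample size rests. Confidence intervals are promised, efficacy is secondary and described as preliminary, and no primary outcome uses McNemar's test.

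A reader might infer more than the documents support:

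- *The plan throws away most of its power.* It does not; the loss is confined to the McNemar analysis. Even there, the uncorrected test keeps more than half of the t-test power (above 39.4%) in 7 of the 24 settings of the wider grid.
- *Many participants will start below any cut-off.* Entry allows this, but the article gives no baseline distribution.
- *The two tests will often disagree.* This was not calculated.
- *PedsQL is affected too.* The sentence covers anxiety scores only.

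**Conclusion.** The point holds in a limited form. As printed, McNemar's test cannot be applied to GAD-7 or SCAS change without a threshold the article does not state, and no rule ranks it against the t test. The sample-size statement supports only the paired t test.

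The mismatch itself needs no assumption. The size of the power loss does: the ranges depend on a correlation and cut-off that are not in the article, and power falls further as the cut-off moves well above the baseline mean. The type I error figures describe what picking the best cut-off could do with the uncorrected test. Nothing in the article says that anyone intends this.

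Because efficacy is a secondary outcome of a 20-person open pilot, this is worth correcting before analysis but does not undermine the trial.

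**What to change.** 1. Delete McNemar's test as a test of score change. State that efficacy is analysed as mean change in the continuous GAD-7 and SCAS total scores, with 95% confidence intervals and a paired t test.
2. If a caseness result is also wanted, fix one cut-off and one time point per scale before data are seen. Then choose one of two forms:
   - a descriptive report of how many baseline cases fall below the cut-off, with an exact 95% confidence interval and no test; or
   - the exact McNemar test on all participants.
3. Do not apply McNemar's test to a subset restricted to baseline cases.

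The cost is analysis wording only. Sample size, assessments and schedule are unchanged.
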